### Intervention Fidelity and Supervision

The study team balanced the clinical and ecological validity of the design and procedures of project Swerve as the intervention was developed for YMSMTG in the DMA. First, we recognize that the CTR and SUBI treatments may have different amounts of contact time with participants. Although it is possible that contact time may influence intervention effects across CTR and SUBI conditions, the control sessions may actually last longer than often expected during CTR, given the high-risk characteristics of our study participants. In our analyses, we will also examine whether length of sessions differ statistically across treatment arms and include time spent in each session as a covariate due to its potential confounder. Second, we recognize that there may be variability in how counselors deliver CTR and SUBI sessions, which could confound our ability to measure the intervention’s strength. We have put in place several procedures to minimize potential biases including training counselors using 2-day training with boosters and ongoing group and individual supervision, allowing counselors at each site—who are not trained in the intervention—to deliver CTR, and monitoring and addressing treatment fidelity for both conditions throughout the trial using the Motivational Interviewing Treatment Integrity-4 rating system [65].

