### Trial Design

The research activities involve a 4-arm factorial RCT of approximately 600 AOD-using YMSMTG aged 15-29 years in the DMA. We will follow participants for 18 months, with follow-up assessments collected every 3 months.

The intervention comprises 2 visits separated by 3 months. Participants are randomized to receive either CTR (control) or a SUBI-adapted version of CTR (referred to as SUBI; intervention) in each visit. To examine how the sequencing and dosing of interventions impacts efficacy, we randomize at baseline into a factorial RCT. The control arm will receive CTR-only at both study visits 1 and 2. Experimental arm 1 (CTR+SUBI) will receive CTR at visit 1 and SUBI at visit 2. Experimental arm 2 (SUBI+CTR) will receive SUBI at visit 1 and CTR at visit 2. Experimental arm 3 (SUBI+SUBI) will receive the intervention condition at visits 1 and 2. Individuals who test HIV-positive at study visits 1 or 2 will receive case management and linkage to care, as offered routinely by each ASO where study activities take place.

This 4-arm factorial randomized design will help answer 3 important questions: (1) what is the impact of adapting current CTR to include SUBI on HIV engagement in care and sexual- and substance-related risk-taking behaviors among high-risk YMSMTG; (2) what combination of services (CTR-only, CTR+SUBI, SUBI+CTR, SUBI+SUBI) has the greatest impact on engagement in HIV prevention (where engagement in care is defined as routine HIV testing for seronegative YMSMTG and linkage and retention in care for seropositive YMSMTG); and (3) if effective, what are the costs of delivering SUBI compared with those of delivering CTR?

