### Randomization

Participants will be randomly assigned to 1 of the 4 conditions using a 1:1:1:1 treatment allocation. The treatment assignments will be generated with the use of a pseudo-random-number generator with permutated blocks that will be used to ensure balance between the numbers of YMSMTG assigned to each treatment. Assignments to the control or intervention arms will use concealment of allocation techniques designed to minimize assignment bias including generating, in advance, the sequence of assignment in sealed envelopes, which will be opened by the counselor at the time of randomization. When YMSM are randomized to receive CTR-only at a visit, they will receive standard CTR (30 min). YMSM randomized to SUBI at a study visit will receive the CTR that has been adapted to include the SUBI. On average, both conditions will last approximately 30 min.

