### Statistical Analysis

Descriptive statistics of the clinical and demographic characteristics of the participants will described for all and by treatment group. These will be compared between treatment groups using *t* tests or Wilcoxon rank sum tests for continuous variables and chi-square tests for categorical variables. We will conduct primary analyses of our pooled successful engagement measure using logistic regression analyses to compare each active treatment group with the control in pairwise comparison tests at an adjusted significance level of .017 to reduce Type-I errors in our 4-arm trial. We will then conduct exploratory logistic regression analyses by sero-status. For seronegative YMSMTG, the proportion of participants who obtain at least 2 tests at least 3 months apart within 15 months will be calculated and presented with corresponding 95% exact binomial CIs. Among seropositive YMSMTG, we will examine how intervention conditions influence HIV linkage and retention in care per IOM guidelines. We will also examine for all participants the pursuit of substance use treatment services (if necessary). Hence, for seronegative participants, the outcome will be repeat HIV testing at regular intervals, and for seropositive participants, the outcome will be linkage and retention in care. We will not consider viral suppression in the regression analysis due to the short time period available to achieve suppression. However, we will present descriptive statistics on viral load and suppression across the 4 treatment arms. The regression will be run with group assignment in the model while controlling for patient, structural, and agency characteristics. Interactions between group assignment and these characteristics will be tested to explore potential moderators of treatment effect. We will repeat these analyses for STI/ATOD biomarkers conducted during the trial. Additional analyses include comparing groups in (1) the average number of tests obtained using Poisson regression and (2) time to getting tested using repeated events survival analysis.

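### Session length arises after randomization, so it cannot confound the arm comparison; using it as a covariate may distort the SUBI effect, and the article leaves unclear which models it enters

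*Protocol article*

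**What the plan says.** Intervention Fidelity and Supervision accepts that session length may not be balanced: "we recognize that the CTR and SUBI treatments may have different amounts of contact time with participants". It adds that "it is possible that contact time may influence intervention effects across CTR and SUBI conditions", and that control sessions may run long because participants are high-risk. It then says that the analyses will test whether length differs across arms and will "include time spent in each session as a covariate due to its potential confounder". The commitment carries no condition, names no outcome or model, and is not called a sensitivity or mediation analysis.

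Three other sections bear on it:

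- Trial Design fixes the order of events: "To examine how the sequencing and dosing of interventions impacts efficacy, we randomize at baseline into a factorial RCT". Its first question asks "what is the impact of adapting current CTR to include SUBI on HIV engagement in care", which is a total effect.
- Randomization expects equal length: "On average, both conditions will last approximately 30 min".
- Statistical Analysis describes the primary comparison as "using logistic regression analyses to compare each active treatment group with the control in pairwise comparison tests" and gives the covariates: "The regression will be run with group assignment in the model while controlling for patient, structural, and agency characteristics". Session length is not among them.

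**The concern.** A confounder must precede, or at least not result from, the exposure. Here the exposure is a two-visit sequence assigned at baseline. Both session lengths arise later, from what is delivered and to whom. The stated reason for the adjustment is therefore wrong.

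The article itself suggests two ways in which the adjustment could do harm. If contact time carries part of the effect, holding it fixed removes that part and the arm coefficient no longer answers the first design question. If participant risk or engagement lengthens sessions and also affects testing or care, conditioning on length opens a non-causal path between arm and outcome. At stake are the size of the reported SUBI effect, the planned power and, in the second case, the type I error that the Bonferroni adjustment is meant to protect.

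**Working it through.** **Inputs from the article.** 1:1:1:1 allocation; 80% power; three comparisons, so two-sided alpha = 0.05/3 = 0.0167; 500 evaluable participants for a 20-point difference and 228 for a 30-point difference (Sample Size and Power; Randomization; Statistical Analysis).

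**Assumed, not in the article.** Control success rate 0.30; within-arm SD of session length 8 min; mean SUBI minus CTR gap *d* of 0, 5, 10 or 20 min; share of the log-odds effect carried by length 0, 0.5 or 1. One length variable stands in for the two sessions.

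**1. Reproduce the plan's sample size.** Per arm, n = [z(1−α/2)·√(2p̄(1−p̄)) + z(0.80)·√(p₀(1−p₀)+p₁(1−p₁))]² / (p₁−p₀)², with z values 2.394 and 0.842.

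- 0.30 vs 0.50: (2.394×0.6928 + 0.842×0.6782)² / 0.04 = 124.3, so 125 per arm and 4×125 = 500.
- 0.30 vs 0.60: (2.394×0.7036 + 0.842×0.6708)² / 0.09 = 56.2, so 57 per arm and 4×57 = 228.

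Both figures match. A control rate of 0.30 with 125 per arm is therefore a fair setting. The true log odds ratio is ln[(0.5/0.5)/(0.3/0.7)] = 0.847.

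**2. Simulate one pairwise comparison.** Logistic regression with and without length, 2,000 replicates per row:

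| Gap (min) | Share via length | Log OR without | Log OR with | SE without | SE with | Power without | Power with |
|---|---|---|---|---|---|---|---|
| 0 | 0 | 0.86 | 0.86 | 0.27 | 0.27 | 0.80 | 0.80 |
| 5 | 0 | 0.85 | 0.85 | 0.27 | 0.28 | 0.80 | 0.75 |
| 5 | 0.5 | 0.78 | 0.43 | 0.26 | 0.29 | 0.73 | 0.19 |
| 5 | 1 | 0.63 | −0.01 | 0.26 | 0.31 | 0.51 | 0.01 |
| 10 | 0 | 0.86 | 0.87 | 0.27 | 0.32 | 0.82 | 0.65 |
| 10 | 0.5 | 0.84 | 0.43 | 0.27 | 0.31 | 0.79 | 0.16 |
| 10 | 1 | 0.78 | −0.01 | 0.26 | 0.32 | 0.73 | 0.01 |
| 20 | 0 | 0.85 | 0.86 | 0.27 | 0.43 | 0.80 | 0.34 |
| 20 | 0.5 | 0.85 | 0.43 | 0.27 | 0.43 | 0.80 | 0.08 |
| 20 | 1 | 0.84 | 0.02 | 0.27 | 0.43 | 0.79 | 0.02 |

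The unadjusted values below 0.85 in the mediated rows arise because, in that model, variation in length dilutes the marginal odds ratio.

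**3. Check by hand at a 10-min gap.**

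- *Precision.* The squared correlation of arm with length is (d/2)²/[(d/2)²+8²] = 25/89 = 0.281. The variance inflation is 1/(1−0.281) = 1.39 and the SE inflation √1.39 = 1.18. Then 0.266×1.18 = 0.314, against 0.316 simulated.
- *Mediation.* With half the effect through length, the direct part is 0.5×0.847 = 0.42, against 0.43 simulated.

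**4. No true effect, shared cause.** Success rate set at 0.50 for an average participant in both arms, correlation of length with a latent cause 0.5, and log odds ratio 0.8 per SD of that cause (all assumed). Within arm, length then predicts log-odds at 0.8×0.5/8 = 0.05 per minute, so adjustment shifts the arm coefficient by roughly −0.05×d, slightly attenuated in a logistic model.

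| Gap (min) | Adjusted log OR | Type I error, adjusted | Type I error, unadjusted |
|---|---|---|---|
| 0 | 0.00 | 0.01 | 0.02 |
| 5 | −0.23 | 0.06 | 0.02 |
| 10 | −0.45 | 0.16 | 0.02 |
| 20 | −0.93 | 0.41 | 0.02 |

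If CTR ran longer, the sign would reverse.

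**5. Missed visit 2.** Sample Size and Power lets participants continue after missing visits. Someone who misses visit 2 has no second session length. Deleting the record loses a randomized participant, coding it as zero turns the covariate into attendance, and imputing it gives a length to a session that did not occur.

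**The case against.** The strongest objection is to scope. The primary model is set out in Statistical Analysis, and session length is not in its covariate list. The commitment sits in a section on fidelity, where it can be read as an additional analysis. This stands in part: a reader might infer that the trial's main result is certain to be adjusted, and the article does not establish that. But the fidelity section refers to the analyses without limit and does not label this one as additional, so the article does not exclude it either.

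The second objection is to size. A reader might infer that SUBI sessions must be longer because they hold more content. The article does not support that. It expects about 30 min for both conditions. Tables 1 and 2 list 7+5 = 12 SUBI steps against 6+4 = 10 CTR steps for a nonreactive result, but 7+4 = 11 against 6+6 = 12 for a reactive one. With equal mean length the simulation shows no harm. This stands, although the fidelity section itself allows that lengths may differ, and with no difference the adjustment has nothing to correct.

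Third, a reader might infer that participants without a second session will be dropped. Complete-case analysis is stated only for the cost-effectiveness primary analysis, and imputation is planned for longitudinal analyses where appropriate. Exclusion is a possible consequence, not a stated one.

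Lastly, separating content from contact time is a legitimate question in a counseling trial. It is a mediation question, however, and needs that label.

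**Conclusion.** Wrong as written. Describing session length as a confounder of a randomized comparison is an error that depends on no assumed figure, and adjusting for it targets something other than the total effect in the trial's first question.

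The consequences are conditional. Loss of precision needs a between-arm difference in mean length. Removal of effect also needs contact time to carry part of it. A false effect needs that difference together with a shared cause of length and outcome. At an assumed 10-min gap and 8-min SD these give, in turn, power of 0.65 instead of about 0.80; a log odds ratio of 0.43 instead of 0.85, with power 0.16; and type I error of about 0.16 instead of 0.0167. At a zero gap the harm is negligible. The article supplies neither the gap nor the SD, so these figures show a range of risk and do not predict the trial's result. It also remains open whether the primary model is affected.

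**What to change.** Delete the confounder rationale in Intervention Fidelity and Supervision and reconcile that section with Statistical Analysis. State that the primary model and every other model of the total effect adjust only for baseline characteristics and exclude session length. Report session length by arm and visit descriptively. Place any question about contact time in a separately labelled exploratory mediation analysis that states its assumptions and how a session that did not take place is handled.

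The cost is about one sentence of analysis wording and no new data. The article reports 142 participants randomized with recruitment ongoing, so the change could be made before outcome analysis.

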### Intervention

Study interventionists will be trained to deliver SUBI and will offer YMSMTG the opportunity to explore and strengthen motivations for changing their ATOD use during session. Interventionists are trained in CTR and typically have a Master’s degree in Public Health, Social Work, or a health-related discipline. The SUBI intervention consists of 2 components. Similar in style to other MI-based brief interventions for substance use and related risk behaviors [50-54], Component 1 focuses on employing MI to explore substance use (illicit drugs, misuse of prescription drugs, alcohol) and co-occurring sexual risk-taking with cultural and developmental tailoring for YMSMTG. There are 7 steps to Component 1 (see Table 1). To maintain the MI spirit, participants are asked for permission to begin the session and also when transitioning through different steps of each component.

**Table 1 table1:** Steps taken during Component 1 of the Swerve intervention compared with standard counseling, testing, and referral (CTR) steps.

Steps	Swerve intervention (SUBI^a^) Component 1: Alcohol, drugs, and sex	CTR: HIV prevention counseling
1	Rapport-building, exploring participants’ strengths and near-term goals	Introduce and orient the participant/client to the session and conduct of HIV test
2	Review of alcohol and substance use and conduct of HIV test	Identify risk behaviors and circumstances
3	Psychoeducation about alcohol/drugs and HIV risk	Identify safer goal behavior
4	Explore benefits to reducing substance use/harm reduction	Identify action steps
5	Build commitment to change	Provide referrals and support
6	Summary of Steps 1-6	Summarize and close
7	Explore possible reactions to HIV test results	—

^a^SUBI: substance use brief intervention.

In Step 1, counselors focus on MI-based engagement strategies to explore areas of strength and aspirations that the participant holds. Affirming these areas allows counselors to build rapport with participants and begin to uncover potential sources of motivation to change risky behaviors.

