We will test for intervention effects over time on sexual risk (eg, CAI events) and drug use (eg, reduction in ATOD use and ATOD-related consequences) outcomes. We will use the general framework of generalized linear mixed models [58-60] to model the longitudinal outcome trajectories [61-63]. Note that some of our outcomes are measured as binary, some as count, and some as continuous measures and thus need to be treated differently. Assuming a linear time trend, visit can be coded from 0 to 7, or it can be simply coded as a categorical variable representing the distinct effect of each visit compared with the baseline. The interaction coefficients are of interest here, measuring the difference in the rate of change in outcomes across the 4 treatment groups. The subject-specific random intercepts *β*_0i_ are assumed to be normally distributed with a common variance and they account for within-person correlation. We will also explore if we need a subject-specific random slope corresponding to visit in the above model. Maximum likelihood estimation will be used for fixed effect parameters. To ensure robustness, we will also apply an exchangeable working correlation structure to its corresponding generalized estimating equation model [64].

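### Counselor appears largely nested within condition, but no described model or sample-size step allows for it; if outcomes cluster by counselor, the SUBI contrasts' standard errors will be too small.

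*Protocol article*

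**What the plan says.** **Who delivers what.** The Intervention section of the protocol article says: "Study interventionists will be trained to deliver SUBI". Under Intervention Fidelity and Supervision, one of the measures against bias is "allowing counselors at each site—who are not trained in the intervention—to deliver CTR". The Intervention section also says: "Interventionists are trained in CTR and typically have a Master’s degree".

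**The threat is named.** The fidelity section concedes that "there may be variability in how counselors deliver CTR and SUBI sessions, which could confound our ability" to measure the strength of the intervention. Its answer is training with boosters, group and individual supervision, separate CTR counselors, and fidelity ratings in both conditions.

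**The models.** Under Statistical Analysis, the primary analysis of pooled engagement is done "using logistic regression analyses to compare each active treatment group with the control in pairwise comparison tests", at an adjusted level of .017. On covariates: "The regression will be run with group assignment in the model while controlling for patient, structural, and agency characteristics". The longitudinal models have subject-specific random intercepts, and "they account for within-person correlation". A random slope for visit will be explored, and a GEE counterpart with exchangeable correlation is added for robustness. Session length is entered as a covariate (fidelity section). Counselor is not mentioned in any model.

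**The sample size.** Sample Size and Power uses a two-sample test of proportions with a Bonferroni adjustment. It requires 500 participants for a 20-point difference and 228 for a 30-point difference, and enrols 600 to allow for 20% loss.

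**The concern.** A counselor not trained in SUBI cannot deliver it. In SUBI+SUBI versus CTR+CTR, the two arms are therefore seen mainly by different people. Any differences between counselors in how far they move participants toward repeat testing then enter the arm contrast and do not cancel. Agency covariates remove differences between sites, not between counselors within a site. Fidelity work may shrink the counselor variance, but it does not correct the standard errors for what remains.

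This is more than detail left to an analysis plan. The article sets the correlation structure at subject level. It also treats its two delivery threats differently: session length is handled in the analysis, counselor variability only operationally.

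At stake are intervals that are too narrow, a family-wise error above the level that the Bonferroni step is meant to protect, and the risk that a few strong or weak counselors are read as an effect of SUBI.

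**Working it through.** **1. The plan's own figures.** Inputs: two-sided alpha 0.05/3 = 0.0167 (z = 2.394), power 80% (z = 0.842), four equal arms. The control rate is not stated; 30% is assumed.

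n per arm = [2.394 × √(2p̄(1−p̄)) + 0.842 × √(p₀(1−p₀) + p₁(1−p₁))]² / (p₁−p₀)²

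- 30% vs 50%: (2.394 × 0.693 + 0.842 × 0.678)² / 0.04 = 124.3, so 125 per arm and 500 in total.
- 30% vs 60%: (2.394 × 0.704 + 0.842 × 0.671)² / 0.09 = 56.2, so 57 per arm and 228 in total.

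Both stated totals are reproduced with independent participants, that is, with a design effect of 1.

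**2. Allowing for counselors, SUBI+SUBI versus CTR+CTR.** From the document: 600/4 = 150 per arm, and 150 × 0.80 = 120 analysed. Assumed, because the article gives neither: k = 4 to 12 counselors per condition, ICC 0.01 to 0.05, counselors fully nested.

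- Design effect (DE) = 1 + (120/k − 1) × ICC
- Standard error multiplier = √DE
- Actual error of the unadjusted test = 2 × [1 − Φ(2.394/√DE)]
- Power (30% vs 50%) of a correctly sized test, using 120/DE per arm

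The simulation used 20,000 runs per cell, a 30% rate in both arms, and the ICC on the logit scale.

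| k | ICC | DE | SE × | Error, formula | Error, simulated | Power |
|---|---|---|---|---|---|---|
| 4 | 0.01 | 1.29 | 1.14 | 0.035 | 0.030 | 65.5% |
| 4 | 0.02 | 1.58 | 1.26 | 0.057 | 0.046 | 55.0% |
| 4 | 0.05 | 2.45 | 1.57 | 0.126 | 0.092 | 35.1% |
| 8 | 0.01 | 1.14 | 1.07 | 0.025 | 0.022 | 71.9% |
| 8 | 0.02 | 1.28 | 1.13 | 0.034 | 0.028 | 65.9% |
| 8 | 0.05 | 1.70 | 1.30 | 0.066 | 0.050 | 51.3% |
| 12 | 0.01 | 1.09 | 1.04 | 0.022 | 0.0185 | 74.2% |
| 12 | 0.02 | 1.18 | 1.09 | 0.0275 | 0.024 | 70.1% |
| 12 | 0.05 | 1.45 | 1.20 | 0.047 | 0.038 | 59.4% |

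Without clustering, 120 per arm gives 78.4% power.

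Example, k = 8 and ICC 0.02: DE = 1 + (15 − 1) × 0.02 = 1.28; √1.28 = 1.13; 2.394/1.13 = 2.12; error = 0.034.

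The simulated errors are lower because a logit-scale ICC is smaller on the scale of proportions. At a 30% rate it is roughly 0.21 × 3.29 × ICC/(1 − ICC), so 0.05 becomes about 0.036.

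**3. Does nesting cause it?** The same simulation with the same counselors delivering both conditions gave errors of 0.015 to 0.017, which is essentially nominal. The inflation comes from having different counselors in the two conditions.

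**The case against.** **Separation is not fully documented.** A reader might infer that CTR and SUBI are always delivered by different people. The text does not go that far. The fidelity section permits untrained counselors to deliver CTR but does not bar SUBI-trained staff from doing so, and interventionists are CTR-trained. The Randomization section has the counselor open the envelope and describes no hand-off. Any overlap reduces the problem, and full crossing removes it. This objection stands, and it makes the point conditional.

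**The ICC might be zero.** The article expects variability in delivery. That is not the same as correlation in engagement up to 15 months after two sessions of about 30 minutes. This also stands. An effect is still plausible, because counselors are trained to encourage repeat testing, which is the primary outcome for seronegative participants.

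**The figures cover one contrast and a simple test.** The mixed arms share CTR counselors with control for one session, so inflation there is probably smaller. Agency covariates in the planned regression may absorb any between-site part of the counselor variance. Both limits stand.

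**This belongs in the analysis plan.** That is true of degrees of freedom or the exact multiple-membership form. It does not excuse naming a threat and then describing models and a sample size that leave it out.

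**Conclusion.** The point holds in conditional form. Counselor appears largely nested within condition, the article itself raises counselor variability, and nothing in its described models or sample size allows for it. If the counselor ICC is above zero, the standard errors of the SUBI contrasts will be too small.

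Under the assumed ranges for SUBI+SUBI versus CTR+CTR, they are understated by a factor of 1.04 to 1.57. The nominal 0.0167 test then has an actual error of about 0.02 to 0.13 by formula, or 0.0185 to 0.092 by simulation. In the middle case of 8 counselors and ICC 0.02 it is about 0.03, roughly twice nominal.

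Two stronger readings are not supported. The upper figure is not an expected value, since it needs 4 counselors per condition, ICC 0.05 and complete nesting together. Nor would a counselor random effect settle the confounding: with counselors nested in condition it can widen the intervals, but it cannot separate counselor skill from SUBI.

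**What to change.** - Record a counselor identifier for every session at visits 1 and 2, and state whether SUBI-trained staff also deliver CTR.
- Pre-specify a counselor-adjusted analysis of the primary and longitudinal models: a counselor random effect, or multiple membership over the two sessions, with a small-sample correction. Make it a named sensitivity analysis, or the primary analysis if counselors are numerous enough.
- Report the number of counselors per condition and the counselor ICC.
- State that the power figures assume no counselor clustering, and that the contrast is SUBI with its counselors against CTR with its counselors.

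**Cost.** One data field, probably already in session records, and a few lines of analysis text. At the article's cut-off 142 of the planned 600 had been randomized, so most sessions were still to come. The intervals will be wider, and with few counselors the variance estimate will be imprecise.
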